### Concealment mechanism {16b}

The treating therapist will be notified by the DRCI (by e-mail) of the treatment allocation. The study database will be pseudo-anonymized (with assignment of patient codes) and held on a server with a secure sockets layer certificate. The two GR programs will be applied during 30-min sessions comprising five 5-min exercises, with a 1-min break between exercises (Tables 1 and 2).

### Implementation {16c}

An investigator at each center will enroll participants, and trained therapists (physiotherapists, occupational therapists, and/or sports therapists) will assign participants to interventions.

## Assignment of interventions: blinding

### Who will be blinded {17a}

SYNCOMOT is an open trial; participants and therapists will therefore not be blinded to the intervention allocation. The assessors of the primary and secondary outcomes will not be blinded.

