### Intervention description {11a}

GR program is based on a personalized, progressive DT approach; with repetitive, goal-oriented tasks. At each site, at least two trained physiotherapists will deliver the intervention in the two parallel groups. The GR sessions will include 30 min of physical therapy on 3 days a week for 4 weeks after inclusion (i.e., 12 sessions in total), instead of the patient’s standard rehabilitation sessions on those days. Each 30-min session will consist of five different 5-min exercises, with 1 min of rest between each exercise. The GR protocols will focus on ST gait or on cognitive-motor DT gait. The patient’s progression through the protocol will be standardized according to the self-assessed cognitive and motor burdens (rated on visual analog scales (VASs)) at the end of each session. If the cognitive or motor burden of the last session is below 7 on the VAS, the intensity in the next session will be incremented by one level. Ideally, the intensity of the patient’s GR will increase week after week. If the patient fails an exercise or session, it will be replaced by the last exercise or session in which the patient was successful. The sessions’ functional task training will combine intensity with functional relevance [16]. The care providers’ adherence to the rehabilitation protocol will be evaluated during study monitoring visits.

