**Neuropsychologist**					
Neuropsychological battery^d^		✓	✓	✓	✓

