**Procedure**: Examiners had to read each proposal to the patient and caregiver and when impairment was detected, the corresponding Rankin grade had to be selected. The examiner might also gather data from other sources, such as records, nurse notes, and medical files. The examiner was instructed to rate what the patient actually did. The only exceptions concerned situations where the patient could clearly perform the activity in a fully independent manner but it was not performed for contextual reasons: patients able to work but not returning to work because the stroke occurred just before retirement (early retirement); patient able to perform basic activities but the carer prefers to do them because of time pressure; patient not confronted with specific activities (complex financial activities, transportation, meal preparation) since hospital discharge

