This study has several complementary strengths. Firstly, the rehabilitation protocols have been designed to increase the degree of synergy between cognitive and motor functions and thus enhance all aspects of the International Classification of Functioning, Disability, and Health core set for stroke (i.e., gait, personal autonomy, social participation, and QoL). This personalized, standardized rehabilitation protocol for gait, balance, and cognitive skills will mix cognitive tasks involving internal interfering factors (via phasic, praxis, executive function, and memory tasks) and tasks involving external interfering factors (spatial cognition) and thus will call upon both low-level and high-level cognitive systems. Moreover, the GR program will use concomitant motor tasks (e.g., a praxis DT with hand engagement) known to have a greater impact on walking, along with complex cognitive tasks involving executive function during gait (e.g., an executive DT with a go/no-go task) [78]. Gait and cognitive performance will be assessed with gold-standard STs: the 10MWT [64] and the French adaptation of the Harmonization Standards Neuropsychological Battery [56]. The same care providers will deliver the intervention in both groups. Our robust assessment of CMI via four complementary cognitive tasks (phasic, praxis, memory, and executive function tasks) and two types of motor activity (gait and dynamic balance) should provide more details about these aspects [79].

The study’s main limitation is its open design: the protocol will not be blinded to the patients or therapists. Secondly, the primary outcome is performance in an ST (gait in the 10 MWT), rather than in a DT. We chose to use the 10 MWT because it is the gold standard for gait performance and is linked to a decline in the elderly [80, 81], post-stroke social inclusion [82], and mortality [11, 64, 83]. After stroke, patients prioritize gait autonomy in their rehabilitation goals [84]. Furthermore, we have found that gait disorders (rather than behavioral and cognitive disorders) are among the main determinants of disability at post-stroke M6 [7]. Although we could have chosen cognitive function as the study's primary criterion, we preferred to focus on walking speed as a marker of walking function [67] but also of survival [11], motor and balance functions, autonomy via community ambulation [85], social participation, and health-related QoL [9, 83, 86].

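### The neuropsychologist who scores the cognitive battery is left unblinded without a stated need, which exposes those secondary outcomes to an avoidable risk of assessor bias of unknown size

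*Protocol article*

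**What the plan says.** **Blinding.** Section {17a} derives from the open design that "participants and therapists will therefore not be blinded to the intervention allocation". It then adds, as a separate sentence without a reason, "The assessors of the primary and secondary outcomes will not be blinded".

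**Who treats.** Section {11a} says that at each site "at least two trained physiotherapists will deliver the intervention in the two parallel groups".

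**Who learns the allocation.** Section {16b}: "The treating therapist will be notified by the DRCI (by e-mail) of the treatment allocation". Section {16c}: "An investigator at each center will enroll participants, and trained therapists (physiotherapists, occupational therapists, and/or sports therapists) will assign participants to interventions".

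**Who rates.** Table 3 groups assessments by staff role.
- The neuropsychologist has one row, "Neuropsychological battery", at M0, M1, M2 and M6. Table 4 lists its content: global cognition, language, praxis, memory, neglect, executive tests, processing speed, a behavioral dysexecutive inventory, and depression and anxiety scales.
- The investigator has NIHSS, Fugl-Meyer, FIM, mRS-SI and QoL-VAS. The same block also holds randomization and the recording of adverse events.
- Therapists have the walking and timed up-and-go tests.

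**What is acknowledged.** The Discussion names the open design as the main limitation and explains that "the protocol will not be blinded to the patients or therapists". Outcome assessors are not mentioned there. The statistical section blinds the statistician.

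**The concern.** Patients and treating therapists cannot be blinded to a rehabilitation program. It does not follow that every rater must know the arm. The neuropsychologist appears in the article only as an assessor, yet is covered by the blanket statement that assessors are unblinded.

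Cognitive performance is a named secondary objective and part of the trial's hypothesis, which expects dual-task training to improve it. A rater who knows the arm and shares that expectation could prompt, time or score slightly in favor of the experimental group. The trial could not separate such a shift from a real effect. Blinding the statistician does not help, because the shift would already be in the recorded scores.

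**Working it through.** **1. Can the role be masked?** The article attaches no figure to this point, so the first check sets the roles side by side.

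| Role (Table 3) | Described as delivering the programs? | Described as learning the arm? | Rates |
|---|---|---|---|
| Therapists | Yes ({11a}) | Yes ({16b}, {16c}) | Walking and timed up-and-go tests |
| Neuropsychologist | No | No | Cognitive battery |
| Investigator | No | Not stated; randomization is in this block | NIHSS, Fugl-Meyer, FIM, mRS-SI; QoL-VAS also collected |

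Section {16a} places randomization after the baseline assessments, so M0 ratings precede allocation. Only M1, M2 and M6 are in question.

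For the neuropsychologist, no described task requires the arm. For the investigator the document is silent on whether the arm is seen, and Table 3 gives a reason to think it may be.

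**2. Which parts of the battery are most exposed?** Trail Making, Stroop, fluency and processing speed are timed or count-based and leave less room for judgment. The depression, anxiety and dysexecutive behavior scales are taken here to leave more. The article does not describe how they are administered, so this ranking is a judgment.

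**3. How much could a shift matter?** The documents give no bias figure. The following is an illustration under assumed values.

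- Patients per arm: 150 included with 10% loss leaves 150 × 0.90 = 135 ({15}).
- Assumed systematic shift toward the dual-task arm: s = 0.1, 0.2 or 0.3 SD, with no true effect.
- z = s / √(2/135), where √(2/135) = 0.1217.
- Rejection rate = 1 − Φ(c − z) + Φ(−c − z), with c = 1.96 for a two-sided 5% test.

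| s (SD) | z | Rate at 5% | Rate at 1% (c = 2.576) |
|---|---|---|---|
| 0 | 0 | 5% | 1% |
| 0.1 | 0.82 | 13% | 4% |
| 0.2 | 1.64 | 38% | 18% |
| 0.3 | 2.46 | 69% | 46% |

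The last column is included because the statistical section says that Bonferroni will be used for multiple testing. It assumes that the correction is spread over the five secondary domains listed in the outcomes section, 0.05 / 5 = 0.01; the article does not say how the correction is applied. With the 140 per group named in {14} instead of 135, the 5% column becomes 13%, 39% and 71%.

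A stricter threshold lowers the false-positive rate but leaves the bias in the estimated difference unchanged.

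**The case against.** **Open assessment is a disclosed choice.** {17a} says so plainly, the Abstract and Discussion call the open design the main limitation, and a condensed article need not give every reason. That is fair, and there is no contradiction here. The Discussion's wording does not conflict with {17a}; it is only less complete. What stands is that the choice covers a role for which no need is apparent.

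**A reader might extend the point to all rater-scored outcomes**, on the ground that investigators do not treat and that only therapists receive the allocation. The documents do not support this. {16b} does not say that only the therapist is told. Table 3 lists randomization and adverse-event recording under the investigator. Under {26a} the center's lead investigator is a rehabilitation specialist, and the patients are in-patients during the program, so the arm may well become known through care. Masking NIHSS, Fugl-Meyer, FIM and mRS-SI without extra raters is therefore not shown to be possible.

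**A reader might also infer that the mRS-SI rater will find the arm in the notes**, since "The examiner might also gather data from other sources, such as records, nurse notes, and medical files". That is the instrument's own procedure, and nothing says that training records are filed there. It is a possible leak, not a demonstrated one.

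**Masking may fail.** Patients can mention their program and small units share information. This stands: masking would reduce the risk, not remove it.

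**The timing is late.** Trial status reports inclusion from March 2017 and expected completion of recruitment in 2023. Masking part-way would mix masked and unmasked ratings over calendar time. This also stands and limits the benefit.

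**Conclusion.** The point holds for the neuropsychologist. The article leaves this assessor unblinded although it describes no task that requires knowledge of the arm, so the cognitive, mood and behavioral outcomes are exposed to an avoidable risk of assessor bias. This rests on the article's silence about any treating or allocation role for neuropsychologists; the full protocol might show otherwise.

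The documents support a risk, not a finding that these outcomes are biased. Size and direction cannot be known from them. The 13% to 69% range depends wholly on assumed shifts of 0.1 to 0.3 SD and an unadjusted 5% test. A single shift across the battery also fits the timed and count-based tests poorly.

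For the investigator-scored scales the supportable conclusion is weaker: mask where feasible, and otherwise say that the ratings are open. Only secondary outcomes are at issue. The therapist-timed walking tests, including the primary outcome, are a separate matter. This is an inexpensive improvement, not a defect that undermines the trial.

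**What to change.** 1. Amend {17a}: neuropsychologists are not told the allocation at M1, M2 and M6.
2. Keep the allocation e-mail and session records (levels, burden scores) with the treating therapists, and ask patients not to mention their program to the neuropsychologist.
3. Have the neuropsychologist record a guess of the arm at M6, to show how well masking held.
4. For NIHSS, Fugl-Meyer, FIM and mRS-SI, withhold the allocation where the existing investigator did not see it at randomization and need not know it. Otherwise state that these ratings are open.
5. Record the masking status of each rating, so that masked and unmasked visits can be told apart.
6. Extend the limitation in the Discussion to name outcome assessors.

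Cost: an amended passage, a study-manual instruction and two short data items (arm guess and masking status). No sample-size change or extra visit is needed, and no extra staff for the neuropsychologist part. The drawbacks are that some raters will be unmasked in practice, and that only visits still to come can benefit. For ratings already made openly, the stated limitation is the only remedy.

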### Procedure for unblinding if needed {17b}

Not applicable.

## Data collection and management

### Plans for assessment and collection of outcomes {18a}

#### The primary outcome measure

The ST 10MWT will be used to compare gait performance in the DT GR and ST GR groups at post-stroke M6. As a single-task assessment of comfortable walking speed during a 10-m walking test, the ST 10MTW is the “gold standard” short-distance test of walking performance in people with stroke [64, 70]. Gait speed is an important determinant of various health aspects, such as vital status, gait ability (balance, mobility limitations, activities of daily living, etc.), and community activities after stroke [11, 61, 67, 71–73].

The ST 10MWT’s psychometric properties are excellent, with strong reliability, construct validity, sensitivity to change across the care continuum after stroke, and excellent clinical test-retest reliability (intraclass correlation coefficients: 0.80–0.99; measurement error: 0.04–0.40) [64]. Gait speed is clinically meaningful and is correlated with measures of strength, balance, and physical activity (*r* = 0.26–0.8, *p* < 0.05) [64]. Each center will receive a training visit and will be given guidelines on performing the ST 10MWT.

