**Methods:**

This multicenter (*n*=12), two-arm, parallel-group, randomized (1:1), controlled clinical study is a superiority trial. With *p*<0.05, a power of 80%, and an expected loss to follow-up rate of 10%, the inclusion of 300 patients will be required to evidence a 0.1-m.s^−1^ gain in gait speed. Trial will include adult patients (18–90 years) in the subacute phase (0 to 6 months after a hemispheric stroke) and who are able to walk for 10 m (with or without a technical aid). Registered physiotherapists will deliver a standardized GR program (30 min three times a week, for 4 weeks). The GR program will comprise various DTs (phasic, executive function, praxis, memory, and spatial cognition tasks during gait) in the DT (experimental) group and gait exercises only in the ST (control) group. The primary outcome measure is gait speed 6 months after inclusion. The secondary outcomes are post-stroke impairments (National Institutes of Health Stroke Scale and the motor part of the Fugl-Meyer Assessment of the lower extremity), gait speed (10-m walking test), mobility and dynamic balance (timed up-and-go test), ST and DT cognitive function (the French adaptation of the harmonization standards neuropsychological battery, and eight cognitive-motor DTs), personal autonomy (functional independence measure), restrictions in participation (structured interview and the modified Rankin score), and health-related quality of life (on a visual analog scale). These variables will be assessed immediately after the end of the protocol (probing the short-term effect), 1 month thereafter (the medium-term effect), and 5 months thereafter (the long-term effect).

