### Eligibility criteria {10}

The inclusion criteria will be as follows: (i) age between 18 and 90, (ii) admission to a rehabilitation department within 6 months of a first ischemic or hemorrhagic stroke with positive brain imaging findings (computed tomography (CT) or magnetic resonance imaging (MRI) of the brain), (iii) ability to provide informed consent, (iv) ability to walk at least 10 m (with or without a technical aid) at a speed below 1.2 m.s^−1^, and (v) social security coverage. The exclusion criteria will be (i) prestroke locomotor or neurological disorders affecting gait, (ii) visual or hearing disorders that impair communication, (iii) severe aphasia, (iv) participation in another interventional study of gait or cognitive rehabilitation, (v) pregnancy or breastfeeding, and (vi) administrative supervision (legal guardianship or incarceration).

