### Outcomes {12}

#### Clinical assessments at baseline (Table 3)

The study population's characteristics recorded at baseline (M0) will include demographic variables (age, sex, and handedness), comorbidities (neuro-orthopedic and bladder disorders), the stroke date, the type of stroke (site, side, and ischemic or hemorrhagic), the stroke severity (National Institutes of Health Stroke Scale (NIHSS) score) [47], neurological impairment (the motor part of the Fugl-Meyer Assessment of the lower extremity [54], the French adaptation of the Harmonization Standards Neuropsychological Battery [50, 55, 56] (Table 4), personal autonomy (the functional independence measure (FIM) [51]), disability (a structured interview with a modified Rankin scale score (mRS-SI) (Table 5) [52]); and QoL on a VAS (QoL-VAS). Qualitative and quantitative gait variables will be assessed with a clinical classification of gait disorders (Supplementary material 1), the single-task 10-m walking test (ST 10MWT) [61], and the FIM's “walking” item [51]. Balance will be assessed in the timed up-and-go (TUG) test. In order to assess CMI, four cognitive-motor DTs will be performed during the DT 10MWT and the DT TUG test: a verbal Trail Making Test (executive function) [59], a symbolic praxis test [60], a literal fluency test [50], and a verbal serial number recall task (short-term memory [62]). The data from the cognitive-motor DTs will be recorded every 15 s, so that participants can be compared regardless of their gait speed [63].

**Table 3 Tab3:** Schedule for the assessment of primary and secondary outcomes

	Recruitment	Inclusion M0	Follow-up visit at M1	Follow-up visit at M2	Follow-up visit at M6

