#### The primary outcome measure

Gait speed is the “gold standard” measure of gait performance [64]. At the subacute stage of stroke, speed was recently estimated to be 0.34 m.s^−1^, i.e., a 70% decrease [53]. The ST 10MWT will be used to assess gait performance in the DT GR and ST GR groups at post-stroke M6. This test is a key indicator of functional gait performance, the risk of falls, and decline after stroke [40, 41]; it constitutes the gold standard for the provision of quantitative data on gait performance. Performance in the 10MWT is known to be related to community ambulation ability and QoL [10, 53, 63–66].

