### Plans to promote participant retention and complete follow-up {18b}

SYNCOMOT is an in-patient protocol; retention is therefore expected to be high because (i) the included patients will be hospitalized in a stroke rehabilitation unit during their GR, and (ii) follow-up at M6 is a routine clinical procedure after stroke. Any deviation from the study protocols will be reported in the e-CRF by training therapists. The Ennov Clinical® data entry software will instantly identify any missing or aberrant data, so that the latter can be completed or corrected as soon as possible. This multicenter, randomized, controlled superiority trial will compare DT versus ST GR programs for all allocated patients with available data, on an intention-to-treat basis.

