## Statistical methods

### Statistical methods for primary and secondary outcomes {20a}

#### Primary outcome measure

The primary outcome measure will be the ST 10MWT result 5 months after the end of the GR protocol. Depending on the type of data and after adjustment for the patient’s age, center and the NIHSS score in an analysis of covariance (ANCOVA), an independent *t*-test, a Mann-Whitney test, or a generalized linear mixed model will be used to compare the two groups with regard to the 10MWT speed.

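### The two sections that define the primary outcome date it from the stroke, while the abstract, Table 3 and the statistical section date it from inclusion; for late entrants the stroke-dated endpoint would precede the end of the program

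*Protocol article*

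**What the plan says.** Two sections of the protocol article define the primary outcome measure, and both date it from the stroke. Outcomes {12}: "The ST 10MWT will be used to assess gait performance in the DT GR and ST GR groups at post-stroke M6". Plans for assessment and collection of outcomes {18a}: "The ST 10MWT will be used to compare gait performance in the DT GR and ST GR groups at post-stroke M6".

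Three other places date it from inclusion, directly or by implication:

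- The abstract (Methods): "The primary outcome measure is gait speed 6 months after inclusion".
- Table 3 labels the inclusion visit M0 and lists the single-task 10-m walk test at M0, M1, M2 and M6.
- Statistical methods {20a}: "The primary outcome measure will be the ST 10MWT result 5 months after the end of the GR protocol".

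Two further statements bear on the point. Eligibility {10} requires "admission to a rehabilitation department within 6 months of a first ischemic or hemorrhagic stroke", and the abstract likewise describes patients 0 to 6 months after stroke. The retention section {18b} expects good follow-up partly because "follow-up at M6 is a routine clinical procedure after stroke".

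**The concern.** Stroke date and inclusion date can lie up to about six months apart, so the two origins name different days for nearly every patient. The primary objective is long-term gait velocity, and the outcome sections equate long term with M6. With inclusion as the origin, every patient is measured at about the same distance from training. With the stroke as the origin, that distance shrinks as entry gets later and finally turns negative, so the measurement could not capture a long-term effect of the program in late entrants. No sentence in the article says which origin prevails, and the wording that fails is in the sections meant to define the endpoint.

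**Working it through.** **Inputs**

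- Program length: 4 weeks from inclusion, i.e. 28 days (Intervention description {11a}); at most 31 days if sessions are rescheduled (section {11b}).
- Entry: 0 to 6 months after stroke (abstract, Eligibility {10}).
- Month length: 365.25 / 12 = 30.44 days, so 6 months = 182.6 days (convention used here).

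**Step 1. Do the inclusion-based statements agree?** Interval from program end to inclusion + 6 months:

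- 182.6 − 28 = 154.6 days = 5.08 months
- 182.6 − 31 = 151.6 days = 4.98 months

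This reproduces the five months in the statistical section. The abstract, Table 3 and the statistical section therefore describe one visit.

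**Step 2. Interval under the stroke origin.** For inclusion at *t* months after stroke:

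interval from program end to the stroke-dated endpoint = 182.6 − 30.44 × *t* − (28 or 31) days

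| Inclusion, months after stroke | Interval, 28-day program (days) | Interval, 31-day program (days) | Inclusion-based M6, months after stroke |
|---|---|---|---|
| 0 | 154.6 | 151.6 | 6 |
| 3 | 63.3 | 60.3 | 9 |
| 5 | 2.4 | −0.6 | 11 |
| 5.5 | −12.8 | −15.8 | 11.5 |
| 6 | −28.0 | −31.0 | 12 |

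Under the inclusion origin the interval is 151.6 to 154.6 days in every row.

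**Step 3. Where does the sign change?** The interval is zero at

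- *t* = (182.6 − 28) / 30.44 = 5.08 months (28-day program)
- *t* = (182.6 − 31) / 30.44 = 4.98 months (31-day program)

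Anyone included later than this would have a stroke-dated endpoint before the program ends. At 6 months it falls on the day of inclusion. Eligibility limits the admission date rather than the inclusion date, so inclusion could be later still.

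**Step 4. How many patients?** The article gives no distribution of entry times, so the share can only be bracketed by assumption.

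- All inclusions before about 5.0 months: 0%.
- Entry uniform over 0 to 6 months: 28 / 182.6 = 15.3% to 31 / 182.6 = 17.0%.

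The planned sample size does not enter this calculation and does not change.

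**The case against.** The strongest reply is that the schedule already settles the date. Table 3 starts its visits at inclusion and lists the walk test only at those visits; the secondary-outcome sections tie M1, M2 and M6 to short, medium and long term; and the statement that governs the analysis fits inclusion plus six months. On that view the stroke-dated phrase is a loose name for the M6 visit. To follow it literally in a late entrant, a site would have to carry out M6 before M1, against the order of the table. Section {18a} also describes site training and a manual covering the visits.

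Much of this stands: inclusion is probably the intended origin. It does not remove the contradiction. The phrase appears in both sections that define the primary outcome, and the Discussion uses the same expression in its ordinary sense when it cites published work on disability. Table 3 itself dates the imaging from the stroke, so both clocks run in one schedule.

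Several stronger readings are tempting but unsupported:

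- **Three conflicting dates.** There are two; the statistical section agrees with the abstract (Step 1).
- **A known, sizeable fraction measured too early.** One might infer a mean of 3.0 months from inclusion to endpoint, about 15% measured before the program ends, and a third (2/6) before M2. All of these require uniform entry, which nothing in the article supports. Screening on admission to the rehabilitation unit is compatible with earlier entry.
- **Sites are using the wrong visit.** The retention sentence gives a reason to expect attendance. It neither defines the endpoint nor tells sites to substitute a routine visit; confusion is possible, but it is inference.
- **The effect is necessarily diluted.** This is plausible for measurements taken before training ends. For shorter positive intervals the effect could be larger or smaller, and the article does not say which.

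**Conclusion.** Wrong as written: an internal inconsistency in the timing of the primary endpoint. The Outcomes section and section {18a} contradict the abstract, Table 3 and the statistical section, and nothing reconciles them. Taken literally, the stroke-dated rule spreads the interval from program end to endpoint from about +5 months to about −1 month over the entry window, and it cannot measure a long-term effect in patients included after about month 5.0 to 5.1. These results rest only on the stated program length and entry window. The number of patients concerned cannot be derived from the article, so the 15% to 17% figure is conditional on uniform entry and does not carry the conclusion. This goes beyond a clerical slip because it is the rule for the primary endpoint, but it does not show that any measurement has been mistimed.

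**What to change.** In the primary-outcome paragraphs of Outcomes {12} and of section {18a}, replace the stroke-dated phrase with: *the M6 visit, six months from inclusion (about five months from completion of the GR program)*. This matches the abstract, Table 3 and the statistical section.

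In the retention section {18b}, add that a routine six-month post-stroke appointment does not replace the trial's M6 visit unless the two dates coincide.

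The cost is a wording amendment and a note to sites. Table 3 already counts its visits from inclusion, so no visit or assessment is added and the sample size is unaffected. A new visit window or an additional covariate is not needed to correct this error.
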